### Data analysis

#### Sample size and power calculations

Spontaneous cessation is difficult to estimate, but population cessation rates suggest that it is between 0.5% and 3% [3]. Studies aimed exclusively at self-quitting unaided attempts have found 6 month abstinent rates of 3% [37] and 4.9% [38]. Lancaster and Stead, in a review of thirteen trials comparing standard self-help with no help [20] found an average 6 month quit rate in the control groups of 5%, with the pooled intervention rate slightly higher. Based on these figures we might expect a 3 month abstinence rate in a control group receiving standard materials to be at the upper limit of estimates of spontaneous long-term abstinence in the population (i.e. 3%).

The Cochrane review [20] of seventeen randomised trials of smoking cessation found that individually tailored materials were more effective than standard and untailored materials (OR 1.42, 95% CI 1.26 – 1.61) where the main outcome was abstinence from smoking after at least 6 months follow-up. The authors report different odds ratios for studies grouped by type, and the range of estimates demonstrate the uncertainty in this area and the need for further research. A range of possible effect sizes that could be used to power the trial are presented in Table 2. To carry out the trial within the resources available, we aim to recruit a sample of 7250. While a sample of this size does not give adequate power at the lower limit, it will give the minimum power required to detect a difference using the midpoint of the range of odds ratios, assuming a two-tailed test and alpha of 0.05 [39].

**Table 2 T2:** Effect sizes and power for different size samples

OR	% increase in cessation rate	Sample	% power
Lower 1.26	3.75	4350	25
		5800	33
		7250	40
		8700	47

Middle 1.42	4.21	4350	54
		5800	67
		7250	77
		8700	84

Upper 1.61	4.74	4350	83
		5800	92
		7250	97
		8700	99

Assuming a cessation rate of 3% in the control group, with the relative increases in the proportion who report continuous abstinence of 3 months or more at a 6-month follow-up in the intervention group, applying the lower, middle, and upper odds ratios of 1.26, 1.42, and 1.61 (and assuming that participants who cannot be contacted at follow up are still smoking)

#### Attrition and Compliance

Based on our previous studies, we expect approximately 20–25% attrition [14,40]. For the main analysis participants who cannot be contacted at follow-up will be assumed to be smoking (intention-to-treat analysis). Previous studies have found that the number of participants in the intervention group who recalled receiving a personal letter at the 6-month follow-up ranged from 64% [21] to 89% [17]. Analysis of the treatment effect will be based on the whole sample.

#### Planned analyses

Chi-squared tests will compare binary outcomes between the intervention and control groups (e.g. for prolonged abstinence of 4 weeks), with logistic regression to take into account any chance imbalance in important baseline characteristics between the groups. Continuous variables (e.g. cognitive changes) will be compared with the two-sample t-test, with multiple regression to account for other important characteristics. Odds ratios and 95% confidence intervals for differences in means or medians (as appropriate) will be quoted.

To address drop-out, the primary analysis will assume that non-responders continue to smoke. Multiple imputation methods will be used as a sensitivity analysis, where predictors of drop-out will be used to impute likely outcomes (SOLAS software).

Because benefits of interventions may differ by general practice, and patients within practices may demonstrate more similarity in their outcome than patients in different practices, multi-level models will be applied to take into account general practice effects (MLwiN software).

Participants will be categorised by socio-economic status, social deprivation and different educational level to explore the effectiveness of the intervention in these groups.

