### Randomization

Those willing to be contacted for future assessment return the completed questionnaire, together with a signed consent form, to the research team at University College London. Randomisation is at the level of the study participants. Upon receipt of the completed questionnaire eligible participants are randomly assigned to one of the two conditions, according to an externally constructed randomisation plan. The general practices represent a clustering variable and to reduce any confounding by practice we are using block randomisation, using blocks of eight (within which the order of assignment will be random), within each practice to allocate patients to each condition to closely balance the numbers. In a large trial such as this, we expect the conditions to be balanced on important predictive factors such as dependence.

However, any imbalances will be controlled for in the statistical analysis. While it is not possible to blind participants to the receipt of a feedback letter, in order to ensure that the researchers in all cases are blind to the allocation of the participant, the feedback is generated by a service administrator. To avoid bias in the outcome assessment, when conducting follow-up interviews by telephone for non-responders the interviewer will be blinded to the allocation of the respondent.

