### Materials

The baseline assessment questionnaire (SBQ) assesses demographic characteristics (including educational and literacy level), intention to quit, motivation, dependence, previous quit attempts, perceived advantages and disadvantages of quitting, self-efficacy and social environment. The baseline data are scanned and entered using FORMIC data capture software, simultaneously creating an SPSS file containing data for analysis, and a data file for producing feedback letters. A computer program temporarily combines these data with the personal data of participants allocated to the Intervention Group, selecting the correct messages from the message library to produce a feedback report. Once the report is produced the file is deleted, in accordance with the Data Protection Act. Participants are informed of this possible use of the data.

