### Outcome measures

Outcomes are to be measured by postal questionnaire. Non-respondents to questionnaires will receive one postal reminder. Non-respondents to the reminder will be contacted by telephone. In order to estimate the accuracy of self-reports, a random sample of 20% of the participants who report abstinence will have their status validated by salivary cotinine sample, obtained by post.

Long term abstinence has been thought of as the gold standard for evaluating smoking cessation interventions, but has been criticized as failing to measure other possible benefits of treatment, such as repeated quit attempts and shorter periods of abstinence [34]. Recent recommendations suggest the use of less stringent criteria of 4-week or 7-day abstinence [35]. Cessation-induction trials test a treatment to prompt cessation among all smokers, including those with low motivation [36], it is important therefore in such trials to measure cognitive change, which can lead to quit attempts, short periods of abstinence, and eventual prolonged abstinence. Six months is widely recommended as the minimum length of follow-up in such trials, and accepted by the Cochrane reviews on smoking cessation.

The Primary Outcome Measure is Prolonged abstinence for 1 month and for 3 months at the 6-month follow-up.

Secondary Measures are 24 hr and 7 day point-prevalence abstinence, quit attempts, changes in motivation and intention to quit, and in cognitions measured at baseline, use of NRT or Zyban, and any contact with advice services or health professionals (group, clinic, telephone, or face-to-face), use of NHS resources and other smoking cessation aids for economic analysis.

Process measures are adherence to advice, perceptions of the feedback reports, perceived personal relevance of the feedback reports.

Performance figures against target figures set by PCTs before and after the intervention will be obtained from General Practices as indicators of activity.

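### The plan for continuous outcomes does not name the outcome's own baseline value as a covariate, nor say whether the t-test or the regression carries the result

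*Protocol article*

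**What the plan says.** Under Planned analyses, the protocol article sets the method for continuous outcomes in one sentence: "Continuous variables (e.g. cognitive changes) will be compared with the two-sample t-test, with multiple regression to account for other important characteristics". The same section plans multi-level models to allow for general practice effects.

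The outcomes concerned are listed under Outcome measures as secondary: "changes in motivation and intention to quit, and in cognitions measured at baseline". The Materials section shows that the baseline questionnaire already captures the matching starting values: "intention to quit, motivation, dependence, previous quit attempts, perceived advantages and disadvantages of quitting, self-efficacy and social environment".

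On imbalance, the Randomization section says that "any imbalances will be controlled for in the statistical analysis". It follows a remark that a trial of this size should be balanced on predictive factors, with dependence as the example.

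No section names the baseline value of the outcome itself as a covariate. None ranks the t-test and the regression, so it is not stated which will be reported as the result for these outcomes.

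**The concern.** When an outcome is measured at baseline and again at follow-up, three analyses are available: compare follow-up values, compare changes, or regress the follow-up value on group and baseline (ANCOVA). ANCOVA is at least as precise as either of the others. It also corrects for a chance difference between the groups at the start. A change score over-corrects for such a difference, because people who start high tend to drift back towards the mean.

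The article names the t-test, gives cognitive changes as its example, and then adds regression for *other* characteristics. On a natural reading the outcome's own baseline value, the strongest single candidate covariate, is left out or left to chance. A promise to control imbalances does not replace it. Adjustment that depends on seeing an imbalance is decided after looking at the data, and it gives up the precision gain when no imbalance is seen.

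At stake is the precision and pre-specification of the cognitive and motivational comparisons. Outcome measures describes measuring cognitive change as important in trials of this type. The planned exploration by socio-economic status, deprivation and education uses smaller groups, where lost precision and chance imbalance are both larger than in the whole sample.

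**Working it through.** **The plan's own figures.** The article gives no SD, effect size or power for any continuous outcome, so there is nothing to reproduce on this exact point. Table 2 concerns the primary binary outcome, and it does reproduce. With 3% in the control group and an odds ratio of 1.42, the intervention odds are 1.42 × 0.03/0.97 = 0.0439, a rate of 4.21%. With 7250 participants split equally and a two-sided alpha of 0.05, power is 78.7% without and 76.9% with a continuity correction, against the stated 77%. With the correction, all twelve cells agree within one point. Table 2 is sound but does not bear on this point.

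**Inputs.**
- Recruited sample: 7250 (Sample size and power calculations), taken as 1:1.
- Attrition: 25%, the upper end of the range under Attrition and Compliance. Analysed: 7250 × 0.75 = 5437.5, about 5438, or 2719 per group.
- Two-sided alpha 0.05, as in the plan's own power calculation; 80% power is chosen here for illustration.
- Correlation r between baseline and 6-month values: **not in the documents**. Assumed 0.3, 0.5 and 0.7.
- Equal SDs at both times; clustering by practice ignored.

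**Variance per person, in units of SD².** Follow-up value alone: 1. Change score: 2(1 − r). ANCOVA: 1 − r². The ratio of ANCOVA to change score is (1 − r²) / [2(1 − r)] = (1 + r)/2.

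**Detectable difference at 80% power, in SD.** (1.96 + 0.842) × √v × √(2/2719) = 0.0760 × √v, where v is the variance above.

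**Power of the change-score t-test where ANCOVA has 80%.** Φ(2.80 × √ratio − 1.96).

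| r | Change variance | ANCOVA variance | Ratio | Detectable, change | Detectable, ANCOVA | Gain | Change-score power |
|---|---|---|---|---|---|---|---|
| 0.3 | 1.40 | 0.91 | 0.65 | 0.090 | 0.073 | 0.017 | 62% |
| 0.5 | 1.00 | 0.75 | 0.75 | 0.076 | 0.066 | 0.010 | 68% |
| 0.7 | 0.60 | 0.51 | 0.85 | 0.059 | 0.054 | 0.005 | 73% |

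Inverting the ratios gives 1/0.65 = 1.54, 1/0.75 = 1.33 and 1/0.85 = 1.18, so ANCOVA is worth an effective sample 54%, 33% or 18% larger.

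If the t-test were applied to 6-month values instead of changes (variance 1), ANCOVA would have 91%, 75% or 51% of the variance at the same three correlations. It is the more precise choice on either reading.

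**Chance imbalance.** The standard error of the baseline difference is √(4/5438) = 0.027 SD, so a 1.96-SE imbalance is 0.053 SD. Given such an imbalance, an unadjusted change-score difference shifts by (1 − r) × 0.053: 0.037, 0.027 or 0.016 SD at r = 0.3, 0.5 or 0.7. ANCOVA removes this shift where the outcome is linear in baseline.

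**The case against.** The strongest reply is that the article already promises adjustment. The sentence that names the t-test also names multiple regression, and the Randomization section says without restriction that imbalances will be controlled for. Motivation, intention and self-efficacy are themselves baseline characteristics, so they fall within that promise if they turn out unbalanced. The word *other* may simply mean other than allocated group, and an exact covariate list is something an article commonly leaves to a fuller document.

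Much of this stands, and it rules out several stronger readings that a reader might infer:

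- *That the unadjusted t-test is the lead analysis.* The article puts the t-test and the regression in one sentence and ranks neither.
- *That baseline adjustment is excluded.* It is not named, which is different from being ruled out.
- *That these results are simply left exposed to imbalance.* Regression and control of imbalances are both planned.
- *That the change-score test is biased.* Under randomisation it is unbiased on average. It shifts only conditionally, given an imbalance that has occurred.

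It is also fair that the 18% to 54% figures compare ANCOVA with a bare change-score t-test. They do not compare it with whatever regression would be fitted. Baseline covariates in that regression could recover part of the gain, or all of it if the outcome's own baseline value were among them.

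What the reply does not remove is this. The test is a stated choice, not an omitted detail. The outcome's own baseline value is nowhere a stated covariate. Adjustment triggered by an observed imbalance does not deliver the precision that pre-specified adjustment gives in every case.

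**Conclusion.** The point holds in a limited form. For continuous outcomes measured at baseline and at 6 months, the article names a two-sample t-test with supplementary regression. It does not say that the outcome's own baseline value enters the regression, or which analysis is the result. A better analysis is available from data already collected.

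The relative gain over an unadjusted change-score t-test is clear, but its size depends on a correlation that the documents do not give. The absolute gain in the full sample is modest. Even a baseline imbalance at the edge of the 95% range would move an unadjusted change-score result by less than 0.04 SD. Only secondary outcomes are involved; the primary abstinence comparison and its power calculation are untouched. This is an inexpensive improvement worth making, not a flaw that threatens the trial's main conclusion.

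**What to change.** Add one sentence to Planned analyses along these lines:

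> The main analysis of each continuous outcome measured at baseline and at 6 months will regress the 6-month value on allocated group and the baseline value of that outcome, within the multi-level model for practice; the adjusted mean difference and its 95% confidence interval will be reported, and the t-test will be descriptive only.

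This settles in advance both the covariate and the analysis that carries the conclusion. It also covers EQ-5D, which is measured at the same two times, where it is analysed as a continuous outcome.

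The cost is one sentence. The baseline values are already collected, the multi-level model is already planned, and neither the sample size nor the primary analysis changes.

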#### Economic and Quality of Life issues

The incremental cost-effectiveness of the individual feedback compared to the control condition will be assessed from the NHS perspective in line with methods recommended by NICE [41]. The costs of administration and generation of the feedback will be estimated along with the basic care package from the application of the trial protocols in the different practice settings. The follow-up questionnaire will ask participants about their use of NHS resources, additional primary care appointments or prescriptions and use of specialist smoking cessation services, and other cessation aids. The data on use from these questionnaires will be combined with national estimates of their long run marginal costs from a variety of sources. Six month quit rate (adjusted for cotinine validation) will be used with appropriate epidemiological and economic modelling techniques to estimate the potential quality of life years gained and future savings in smoking related health care costs. The primary analysis with extensive sensitivity analysis including bootstrapping and the use of cost effectiveness acceptability curves will be to assess the cost effectiveness of the intervention compared to the control. However, the data from the trial will also be used to model the overall immediate costs of implementing the intervention in GP practices (including any increased use of other smoking related services) for different types of practices (e.g. in high and low deprived areas) and for England as a whole. Modelling will also be undertaken of the population levels effects on the health of the population and the NHS (including allowance for future savings in NHS costs) and how this intervention may interact with other policy initiatives.

In accordance with NICE technical appraisal guidelines [41], we are using EQ-5D at baseline and at follow-up to investigate short-term quality of life changes. Quality and quantity of life issues will be addressed as part of further modelling of longer-term improvement effects.

### Consumer Involvement

Small groups of smokers recruited via the Quitline commented on the original questionnaire and feedback letter, which were modified accordingly. The smoking cessation counsellors at the Quitline also provided input. Ongoing research using Focus Group discussions with smokers have explored consumers' views on the acceptability of this approach to encourage and support smoking cessation. Follow-up questionnaires sent to all participants in the study will evaluate users' perception of the materials. Participants will have the opportunity to request a report of the results. A lay summary will be prepared and sent to all participants requesting one.

## Discussion

In the UK there are 450 new smokers every day [42]. At this rate of recruitment to the smoking population, there is an urgent need to develop and deliver cost-effective interventions to the bulk of the population, rather than to the minority of dependent smokers who seek specialized help [43].

It is important to offer a range of interventions that appeal to different individual needs and preferences [44]. Computer tailored personal feedback, adapted to reading levels and motivation to quit, is a simple and inexpensive intervention which could be widely replicated and delivered cost effectively to a large proportion of the smoking population. The current portfolio of NHS services does not include a highly tailored approach for smokers who do not wish to attend clinics or have face-to-face counselling.

Reaching and changing the behaviour of smokers, particularly heavily dependent smokers and those from lower socio-economic groups is a challenging task, and the effect of any intervention likely to be small. However, contrary to common assumptions, the proportion of hardcore smokers (defined by cigarette consumption and time from waking to first cigarette), forms a lower proportion of all smokers than in 1996 [45]. Although, the prevalence of smoking by socio-economic group remains unchanged, there are no differences by socio-economic group or by cigarette consumption in intentions and desire to quit and in attempts to quit [45], suggesting that these harder to reach groups will be as receptive to help and encouragement as higher socio-economic groups and less dependent smokers. Furthermore, a modest success rate could have a large effect on public health given its recruitment potential, and make a valuable contribution to lowering smoking prevalence.

Brief advice from GPs has been shown to increase quit rates [46], and this method enables the standardised collection of relevant information from smokers by practice nurses or other health professionals, and could offer an efficient tool to integrate smoking cessation counselling into a busy primary care practice. The degree of uptake by GPs of this intervention is an important issue requiring research in its own right. However, feedback from general practices will inform the degree of uptake as well as reasons for agreeing or refusing to take part in the study, and also identify any potential barriers to the implementation of the intervention. The provision of this option to smokers in primary care could complement existing services, and work synergistically with other measures to produce more quitters and reduce the prevalence of smoking in the UK. This is also an intervention that would fit into the broader scope of tobacco control, by prompting more quit attempts, and increasing referrals to specialised services.

## Abbreviations

EQ-5D: EuroQol 5D; ESCAPE: Effectiveness of computer-tailored Smoking Cessation Advice in Primary Care; GP: General practitioner; GPRF: General Practice Research Framework; MLwiN: Multilevel modelling for windows; MRC: Medical Research Council; MREC: Main Research Ethics Committee; NHS: National Health Service; NICE: National Institute for Clinical Excellence; NRT: Nicotine replacement therapy; PCT: Primary Care Trust; R&D: Research and Development; SBQ: Smoking Behaviour Questionnaire; SOLAS: Software Tool for Analyzing Incomplete Data; SPSS: Statistical Package for the Social Sciences; TTM: Transtheoretical model; UCL: University College London; UK: United Kingdom.
